### Strategies to improve adherence to interventions {11c}

Not applicable. Participation in the study does not require any change in usual care pathways and these will be maintained for all the study arms.

### Relevant concomitant care permitted or prohibited during the trial {11d}

Not applicable. Participation in the study does not require any change in usual care pathways and these will be maintained for all the study arms.

### Provisions for post-trial care {30}

There is no anticipated harm and compensation for study participation.

### Outcomes {12}

#### Primary outcome

The primary endpoint of the study is the serum lactate peak (Lmax) (mmol/l) detected during CPB. The mean of this value will be compared between the three groups of treatment.

#### Secondary outcomes

The area under the curve (AUC) of the serum lactate values measured during CPBNumber of cases with serum lactate peak > 3 mmol/l during CPBEvaluation of intraoperative cerebral perfusion (through monitoring of NIRS)Intraoperative pulmonary perfusion (through Pa/Fi ratio, paO_2_, paCO_2_ at ABG and VO_2_R and DO_2_ of CDI)Evaluation of intraoperative and postoperative low cardiac output syndrome (through the calculation of VISmax)Postoperative and 30-day LVEF (%)Evaluation of pulmonary injury (through the LIS)Postoperative and 30-day Acute Kidney Injury (according to AKIN score)Postoperative gastrointestinal ischaemiaHepatic function and coagulation indexesEvaluation of neurological dysfunction (as dichotomous variable) and evaluation through mRS (0–6) in case permanent neurological injuryIn-hospital mortality and at 30 days from surgeryRe-hospitalization

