#### Secondary objectives

To assess the intraoperative outcomes, through the following perfusion parameters:Intraoperative cerebral perfusion (through monitoring of the NIRS values)Intraoperative pulmonary perfusion (through Pa/FiO_2_ ratio, paO_2_, paCO_2_ at blood gas analysis, and VO_2_R and DO_2_ at CDI® Blood Parameter Monitoring System 550)

To assess postoperative clinical outcomes, through the following parameters:Intraoperative and postoperative low cardiac output syndrome (according to the values of vasoactive inotropic score, VIS) [22]Postoperative cardiac function (measuring left ventricular ejection fraction, LVEF)Postoperative respiratory failure (through the values of Lung Injury Score, LIS, scale) [23]Postoperative stroke and entity of transitory or permanent neurological damage (through score of modified Rankin Scale—mRS) [24]Postoperative acute kidney injury (through AKI score)Postoperative hepatic failure (measuring the hepatic function and coagulation indices)Postoperative gastrointestinal ischaemiaPostoperative cardiovascular death, or death due to other causes

To assess clinical outcomes at 30 days from surgery:Stroke and entity of the transitory or permanent neurologic damage (mRS score)Acute kidney injury (AKI score)Cardiac function (LVEF)Re-hospitalizationDeath for cardiovascular or other causes

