### Intervention description {11a}

The patients enrolled to elective cardiac surgeries will be evaluated during a pre-operative outpatient visit and widely informed about the chance to participate in the study. When patients undergo to the elective surgery general anaesthesia is administered and CPB is installed. The nominal flow for each patient will be 2.4 l/min/m^2^.

A continuous monitoring of blood pressure will be performed invasively by cannulating the radial or femoral artery, as is customary in cardiac surgery.

To keep the MAP values around those corresponding to the randomized group, vasodilator (if MAP overcomes the assigned MAP value) or vasoconstrictor drugs will be used (if MAP value is lower than the assigned group). The following drugs will be used: nitroglycerine at incremental dose of 0.01 mcg/kg/min for a vasodilator effect and norepinephrine at incremental dose of 0.01 mcg/kg/min for a vasoconstrictor effect. The treatment groups will be:

*Group 1: Standard MAP*: MAP values between 50 and 60 mmHg as control group.

*Group 2: High MAP*: MAP values between 70 and 80 mmHg.

*Group 3: Patient-tailored MAP*: MAP comparable to the patient’s pre-operative MAP. This one will be calculated by performing 3 blood pressure measurement in three different moments of the day before surgery (at 8 am, at 3 pm and at 9 pm), and will be calculated using the standard formula “Diastolic AP + 0.33 × (systolic AP − Diastolic AP)”. The preoperative MAP value obtained will be target during CPB, within a range of ± 10 mmHg.

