- Intraoperative (postoperative day, POD, 0)A continuous monitoring of blood pressure will be performed invasively by cannulating the radial or femoral artery, as is customary in cardiac surgery. Data of MAP will be recorded at the beginning of CPB, every 20 min until minute 300 and at the end of CPB.ABG after orotracheal intubation, at the beginning of CPB, every 20 min during CPB (eventually until minute 300), at the end of CPB, at the end of surgery. Data collected: lactates as organ perfusion index, Hb and Hct.Real-time and continuous monitoring of respiratory gases during CPB suggestive of the perfusion trend, through CDI ® 550 Blood parameter monitoring system (Terumo Europe) [25], data collection related to oxygen delivery (DO_2_), oxygen consumption (VO_2_) and oxygen extraction (O_2_ER), at the beginning of CPB, every 20 min (until minute 300) and at the end of CPB.Intraoperative monitoring of Near-Infrared Spectroscopy NIRS [26] defined as non-invasive measurement of cerebral microcirculatory blood flow. Data will be collected at anaesthesia induction, before skin incision, at the beginning of CPB, every 20 min (until minute 300), at the end of CPB and at the end of surgery.Monitoring of CPB and aortic cross-clamp timesCalculation of “vasoactive inotropic score” (VIS) [22] which relates the entity of inotropic and or vasoactive support. VIS max is obtained through the following calculation: [Dopamine dose (mcgkg/min)+ Dobutamine dose (mcg/kg/min) + 100 × Epinephrine dose (mcg/kg/min) + 50 × Levosimendan dose (mcg/kg/min) + 10 × Milrinone dose (mcg/kg/min) + 10,000 × Vasopressin dose (units/kg/min) + 100 × Norepinephrine dose (mcg/kg/min)]. The VIS will be calculated according to the length of surgery.Monitoring of nitroglycerine dose during surgery

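### Intraoperative VISmax is read as low cardiac output, yet it counts the norepinephrine titrated on bypass to reach the assigned MAP, which favours a higher score in the high-MAP arm than in the standard arm

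*Protocol article*

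**What the plan says.** Four statements in the protocol article bear on this.

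- **Construct and instrument.** Secondary objectives names "Intraoperative and postoperative low cardiac output syndrome (according to the values of vasoactive inotropic score, VIS", and Secondary outcomes repeats it as "intraoperative and postoperative low cardiac output syndrome (through the calculation of VISmax". No other criterion for low output is given.
- **Formula and window.** The intraoperative list under Procedures defines VIS as a weighted sum of drug doses that includes "100 × Norepinephrine dose (mcg/kg/min". It adds that "The VIS will be calculated according to the length of surgery". Time on bypass is not excluded. Nitroglycerine is not a term of the score; its dose is monitored as a separate item.
- **How the arms are created.** Under Intervention description {11a}, "vasoconstrictor drugs will be used (if MAP value is lower than the assigned group", and the drug named is "norepinephrine at incremental dose of 0.01 mcg/kg/min for a vasoconstrictor effect". Nitroglycerine is given when MAP is above the assigned value. The control arm has "MAP values between 50 and 60 mmHg as control group", the high arm 70–80 mmHg, and the tailored arm the patient's own preoperative MAP ± 10 mmHg.
- **Flow.** The same section sets a nominal pump flow of 2.4 l/min/m² for each patient.

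The Postoperative list separately includes a VISmax calculation.

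**The concern.** During bypass the pump supplies the flow. Norepinephrine given to bring MAP into the randomized range is then the dose of the intervention and says nothing about how well the heart is pumping. A score that counts this drug and is labelled low cardiac output partly measures the intervention itself.

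The effect runs one way: raising MAP adds points and lowering it adds none. Because the endpoint is a maximum, one on-pump peak can fix a patient's value. At stake is a between-arm difference in a secondary safety outcome that would be reported as low output in the high-MAP arm without any difference in cardiac function.

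**Working it through.** **Figure to reproduce.** The article states no figure for VIS. The only planned number used below is 300 patients per arm (Sample size {14}). It reproduces: with difference 0.19, SD 0.7, two-sided alpha 0.05/3 and 80% power, the two-sample formula gives 285. Dividing by the Mann-Whitney efficiency 3/π gives 285 × π/3 = 298.5, against 300 stated.

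**Step 1: points per titration step.** The weight is 100 and the step is 0.01 mcg/kg/min, both from the article.

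- One norepinephrine step: 100 × 0.01 = 1.0 VIS point.
- Any nitroglycerine dose: 0 points, since the formula has no such term.

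**Step 2: direction, high versus standard.** Take one patient with a given untreated MAP on bypass and apply the stated rule in each arm.

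| Untreated MAP (mmHg) | Standard arm, 50–60 | High arm, 70–80 | Norepinephrine term of VIS |
|---|---|---|---|
| Below 50 | Norepinephrine | Norepinephrine, to a higher target | Higher in high arm |
| 50 to 60 | Neither drug | Norepinephrine | Higher in high arm |
| Above 60, below 70 | Nitroglycerine | Norepinephrine | Higher in high arm |
| 70 to 80 | Nitroglycerine | Neither drug | Zero in both |
| Above 80 | Nitroglycerine | Nitroglycerine | Zero in both |

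The norepinephrine term is never lower in the high arm, and it is higher whenever untreated MAP is below 70. This assumes that the rule is followed and that a higher target needs more drug.

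**Step 3: direction, tailored arm.** For a preoperative MAP of P the band is P − 10 to P + 10. It lies wholly above the standard band only if P − 10 > 60, that is P > 70. It starts at or above the top of the high band only if P − 10 ≥ 80, that is P ≥ 90. The article gives no distribution of preoperative MAP, so the direction for this arm is not fixed.

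**Step 4: what a shift would do (illustration on assumed inputs).** Approximate power for a two-arm comparison is Φ(shift / (SD × √(2/300)) − 1.96), at two-sided alpha 0.05. Shifts of 1, 2 and 5 points correspond to assumed mean norepinephrine differences of 0.01, 0.02 and 0.05 mcg/kg/min. For a shift of 1 and SD of 5: 5 × √(2/300) = 0.408; 1/0.408 − 1.96 = 0.49; Φ(0.49) = 0.69.

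| Assumed VIS SD | Shift 1 | Shift 2 | Shift 5 |
|---|---|---|---|
| 3 | 98% | about 100% | about 100% |
| 5 | 69% | 99.8% | about 100% |
| 8 | 33% | 87% | about 100% |

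Each cell is the chance of a significant difference with identical cardiac function. The calculation lets the dose difference pass in full into VISmax, which holds only where the on-pump period sets the maximum. It is a normal approximation for two arms and stands in for the planned three-group ANOVA or Kruskal-Wallis test.

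**The case against.** The overlap between intervention and score is in the text, but several limits are fair.

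- **Rank of the endpoint.** It is one of many secondary outcomes in a trial that calls itself exploratory. Lmax and the sample size do not depend on VIS. This stands, and it lowers the severity.
- **Other cardiac evidence.** Postoperative VISmax, LVEF at POD 4 and at 30 days, and cardiovascular death are also collected. A reader might infer that the trial is set to conclude that a higher MAP harms the heart. The article does not support that: an intraoperative VIS difference would be read beside these measures, and the bypass MAP target no longer calls for norepinephrine after surgery.
- **Both higher-pressure arms.** A reader might also infer that the tailored arm must score higher by construction. Step 3 shows that this depends on preoperative MAP, which is not given.
- **Size.** Shifts of 5 to 20 points could be obtained by assuming dose differences of 0.05 to 0.2 mcg/kg/min, but no passage supports such doses. Only the 1 point per step comes from the article.
- **Window.** The sentence on length of surgery is loosely worded and could describe a window, a schedule or a scaling. Counting on-pump doses is the natural reading, since the outcome is called intraoperative and nothing is excluded, but it remains a reading.

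The objection that this is detail for the full protocol or SAP does not stand. The article fixes the construct, the score, its weights and an intraoperative period, and following them as written gives a misleading comparison.

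**Conclusion.** The point holds for the intraoperative part of the endpoint, and for any single maximum that includes time on bypass. In the high-versus-standard comparison, VISmax is expected to be higher in the high arm with no difference in cardiac function. The exact part is 1 VIS point per 0.01 mcg/kg/min of norepinephrine and 0 for nitroglycerine. The total shift cannot be computed from the article; the percentages above rest on assumed shifts and SDs.

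The Discussion makes a real effect plausible. It reports difficulty in holding the assigned range, with vasoplegia in the high arm and hypertension in the standard arm, which are the situations that call for norepinephrine in one and nitroglycerine in the other.

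This should be fixed, as a secondary-endpoint matter. The primary endpoint is unaffected, and the planned postoperative VISmax does not share the direct circularity.

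**What to change.** 1. Base the between-arm comparison of low cardiac output on the postoperative VISmax already planned. Where timed dose records allow, VISmax from separation from bypass onward may be used instead.
2. Do not label on-pump VIS as low cardiac output.
3. Report intraoperative norepinephrine and nitroglycerine by arm as delivery of the intervention.
4. Where component doses are available, add a VIS without the norepinephrine term as a sensitivity analysis.

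No treatment rule changes. The cost is a revised outcome definition and a derived variable. No interim analysis is planned and recruitment is expected to run to 31/12/2026, so the change can be fixed before the analysis.

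The intraoperative part of the endpoint is lost or restricted. The article does not say that norepinephrine is recorded by time or split into on-pump and off-pump doses, and recruitment began in 2021, so a post-separation score may not be recoverable for patients already enrolled; postoperative VISmax is the safer choice. An infusion started on pump may also carry over into the early post-bypass period, so some residual overlap should be acknowledged.

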### Participant timeline {13}

The patient will participate to the study from the preoperative day (when he/she will sign the informed consent) until the 30th after surgery. Figure 1 shows all the interventions and data collection timeline.

**Fig. 1 Fig1:**
[figure not shown]
Flowchart of the study

### Sample size {14}

The sample size has been calculated for the primary endpoint: the maximum serum lactate value (Lmax). A preliminary analysis was performed on a sample size of 128 consecutive patients undergone to elective cardiac surgery at Cardiac Surgery Division at AOUI of Verona (about the 10% of the annual volume cases at our Institution). All patients were treated with standard MAP (standard of care) and the estimated mean of Lmax during CPB was 1.25 mmol/l, with a standard deviation of 0.7 mmol/l. Starting from this value, a reduction of −15% of the mean Lmax was considered clinically significant for every comparison that will be performed in the study, as listed below:Standard MAP vs High MAP (−15%) difference *d*=−0,19Standard MAP vs patient-tailored MAP (−15%) difference *d*=−19High MAP vs patient-tailored MAP (−15%) difference *d*=−19

Based on these assumptions, performing the Mann-Whitney non-parametric test and considering an alpha of 0.05 s. Bonferroni for all the three comparisons (corrected Alpha= 0.01667) and a power of 80%, 300 patients should be enrolled for each group, for a total of 900 patients (PASS 14). To account for a potential drop-out of 10%, the size becomes 333 patients per group, then a total of 999 patients. The number of patients that each Participating Centres should recruit has been calculated based on the annual cases volume of each Centre, as follows:

Cardiac Surgery Division of AOUI Verona: 327 cases (109 per group)Cardiac Surgery Division of Ospedale Maggiore di Parma: 162 cases (54 per group)Cardiac Surgery Division of Azienda Sanitaria Universitaria Friuli Centrale di Udine: 231 cases (77 per group)Cardiac Surgery Division of Hospital Clinic de Barcelona, Spain: 279 cases (93 per cases)

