#### Trial design {8}

The present study is an exploratory randomized controlled three parallel-group trial. The patient allocation is 1:1:1. The outcome of patients undergoing cardiac surgery and treated with a MAP standard during CPB is compared to patients treated with high MAP and patient-tailored MAP during CPB.

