### Statistical methods

#### Statistical methods for primary and secondary outcomes {20a}

Demographic and clinical characteristics will be presented as percentage in case of ordinal variables and as percentages, means, medians and standard deviations and/or interquartile range in case of categorical and/or quantitative variables. The Pearson *χ*^2^ and the *H*-test by Kruskal-Wallis will be used for any assessment of differences between the three groups. To evaluate the primary endpoint of the study, the Mann-Whitney test will be used for comparisons between groups with an alpha equal to 0.01667. The Mann-Whitney test will also be used to evaluate the secondary endpoint obtained by AUC, while the Pearson *χ*^2^ will be used to compare the proportion of cases above and below the serum lactate peak cut-off > 3mmol. To compare the secondary endpoints in the three groups according to the types of variables, ANOVA or non-parametric *H*-test by Kruskal-Wallis will be used for quantitative variables, while the Pearson *χ*^2^ test will be performed for dichotomous or categorical variables. ANOVA for repeated measures, or Friedman test or the mixed effects model will be used for variables collected at different timepoints. A *p*-value < 0.05 will be considered statistically significant. Both an intention to treat (ITT) and per protocol (PP) analysis will be performed.

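### Testing all three primary pairs at a fixed 0.01667 is valid but gives up power that a closed procedure for three groups recovers; the planning differences also need correcting and clarifying

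*Protocol article*

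**What the plan says.** In the protocol article, section Sample size {14}, the planning data come from 128 patients who all had standard MAP: "the estimated mean of Lmax during CPB was 1.25 mmol/l, with a standard deviation of 0.7 mmol/l". A 15% reduction "of the mean Lmax was considered clinically significant for every comparison that will be performed in the study". The list that follows gives a difference for each pair: -0,19 for standard versus high, and -19 for both standard versus tailored and high versus tailored. The error rate is split as "Bonferroni for all the three comparisons (corrected Alpha= 0.01667) and a power of 80"%, and the result is "a power of 80%, 300 patients should be enrolled for each group", or 333 per group and 999 in total after 10% drop-out.

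Section Statistical methods for primary and secondary outcomes {20a} carries the same rule into the analysis: "the Mann-Whitney test will be used for comparisons between groups with an alpha equal to 0.01667". Neither section names a step-down or closed procedure. Section Trial design {8} calls the trial exploratory, with 1:1:1 allocation.

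**The concern.** Two things stand out.

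First, the level 0.01667 is applied to all three pairs whatever the other tests show. With exactly three groups this is stricter than family-wise control at 5% requires, so the trial gives up power on its primary endpoint.

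Second, the planning differences are unclear. Two are misprinted. All three carry the label -15%, although 0.19 is 15% only of the standard-MAP mean. High versus tailored has a different reference mean if high MAP works, and this is the comparison that separates the two experimental strategies. A reader cannot tell which effect the 80% refers to there.

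**Working it through.** **1. The plan's own figure.** Inputs from Sample size {14}: mean 1.25, SD 0.7, 15% of 1.25 = 0.1875 (rounded to 0.19), alpha 0.05/3 = 0.01667, power 80%. Two-sided testing is assumed, because it is not stated and one-sided testing would give only 252 per group. Normal data are assumed for the Mann-Whitney efficiency of 3/π = 0.955.

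n = 2(SD/d)²(z_α/2 + z_β)² = 2(0.7/0.19)²(2.394 + 0.842)² = 284.2 per group. Dividing by 0.955 gives 297.6, so 298 (299 with a t-based calculation), against 300 stated. With the unrounded 0.1875 it is 306. Power at 300 per group is 80.4% for 0.19 and 79.2% for 0.1875. The same d applies to every pair, so this covers high versus tailored too. It also shows that -19 is a lost decimal: 300 follows from 0.19.

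**2. Why a fixed 0.01667 is stricter than necessary.** The three null hypotheses (equal Lmax distributions in each pair) are linked, since any two of them imply the third. The only joint null hypothesis is therefore that all three groups are equal. Closed testing then needs two steps: reject the all-equal hypothesis at 5%, then test each pair at 5%. Two ways to do this are:
- Shaffer: the smallest p-value is tested at 0.01667; if it passes, the other two are tested at 0.05.
- Kruskal-Wallis at 0.05; if it passes, each pair is tested at 0.05.

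**3. Size of the gain.** Simulation: 3,000 runs, 300 per group, normal data, SD 0.7. Entries are rejection rates in %; means are standard/high/tailored.

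| True means | Quantity | Bonferroni | Holm | Shaffer | Kruskal-Wallis gate |
|---|---|---|---|---|---|
| 1.25/1.0625/1.0625 | standard vs high | 79.1 | 82.1 | 85.6 | 87.2 |
| same | standard vs tailored | 79.9 | 82.8 | 86.3 | 87.9 |
| same | high vs tailored (false positive) | 1.7 | 4.0 | 5.5 | 5.5 |
| 1.25/1.0625/0.903 | standard vs high | 78.4 | 88.9 | 89.4 | 89.4 |
| same | high vs tailored | 62.9 | 76.7 | 77.4 | 77.4 |
| all equal | any false positive | 4.2 | 4.2 | 4.2 | 5.0 |

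The simulation error at 5% is √(0.05 × 0.95/3000) = 0.4 points, so 5.5% is compatible with 5%. A separate run of 4,000 gave 64% and 79% (Bonferroni and Shaffer) for high versus tailored in the stepped case. For Shaffer it gave a family-wise error of 3.5% with all groups equal and 4.9-5.3% with one true null. Taken together, the gain for that comparison is from about 63% to about 78%.

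**4. What 15% means for high versus tailored.** Assume that high MAP achieves its planned fall: 0.85 × 1.25 = 1.0625. A further 15% fall gives 0.903, a difference of 0.159; 0.19 would be 0.19/1.0625 = 17.9%. Bonferroni power is Φ(d/SD × √(300 × 0.955/2) − 2.394), where the root is 11.97.
- SD fixed at 0.7: 0.1594/0.7 × 11.97 = 2.73; Φ(0.33) = 63%.
- SD proportional to the mean (0.7/1.25 = 0.56): SDs 0.595 and 0.506, pooled √((0.354 + 0.256)/2) = 0.552; 0.1594/0.552 × 11.97 = 3.46; Φ(1.06) = 86%.
- Lognormal data with the same constant ratio of SD to mean: 90-91% by simulation.

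**The case against.** The case against is substantial, and most of it stands. Bonferroni controls the family-wise error, is applied in the same way in both sections, and was already paid for in the 300 per group. The trial calls itself exploratory. Choosing the simpler method is no error.

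A reader might infer that the 80% fails for high versus tailored, or that the trial is too small. The documents do not support this. The plan lists an absolute difference, and at 0.19 every pair has about 80%. They give no mean or SD for either new arm, so the 63% rests on assumptions. It is also fragile: a normal distribution with mean 0.903 and SD 0.7 puts Φ(−0.903/0.7) = Φ(−1.29), about 10%, of lactate values below zero.

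A reader might also infer that the three differences contradict each other, because two equal falls from standard leave no difference between the new arms. They are better read as minimum relevant differences, powered one pair at a time, and not as a joint forecast. Nor does the plan say that it would read a null high-versus-tailored result as equivalence.

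The gain also depends on the data. With lognormal values and SD proportional to the mean, Bonferroni power is already about 90%. Shaffer then gives about 94-95% with equal new arms, and 96% for high versus tailored in the stepped case.

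What remains is that a better procedure is available without extra patients, and that the wording of the planning differences needs repair.

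**Conclusion.** The point holds as an efficiency improvement plus a wording correction. The fixed 0.01667 is valid but needlessly conservative for three groups. Under the plan's SD of 0.7, normal data and 300 per group, a closed procedure gains about 6-8 percentage points per true comparison when the new arms are equal, and about 15 points for high versus tailored in the stepped case, with family-wise error at about 5%. The gain is smaller if lactate is skewed and its SD falls with the mean.

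The two -19 entries change no result. The 80% claim is correct at 0.19 mmol/l for all three pairs. For a 15% fall from an assumed high-MAP mean of 1.06, Bonferroni power would lie between about 63% and 86% or more, depending on the SD.

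**What to change.** 1. In Statistical methods {20a}, replace the fixed 0.01667 with one closed procedure, chosen in advance: Shaffer's step-down (smallest p-value at 0.01667, then the other two at 0.05), or Kruskal-Wallis at 0.05 followed by pairwise Mann-Whitney tests at 0.05. Shaffer has the advantage that it rejects everything that Bonferroni would reject. Kruskal-Wallis is already among the plan's tests.
2. Make the change before any unblinded comparison. No interim analysis is planned, and recruitment is expected to run to 31/12/2026.
3. In Sample size {14}, correct both -19 entries to -0.19. State that 0.19 mmol/l is 15% of the standard-arm mean for all three pairs and that the 80% refers to this absolute difference. If a relative fall from a lowered high-MAP mean is mentioned, give the power range with its SD assumptions.
4. Keep 300 evaluable patients per group and 999 in total.

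Cost: an amendment to the wording, no extra patients, and simultaneous confidence intervals that are less simple than Bonferroni intervals.
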